### SET

The SET program follows the 2019 American Heart Association (AHA) scientific statement on optimal exercise programs for patients with PAD [19]. Each participant completes 36 supervised sessions delivered three times per week over 12 weeks, with each session lasting 60 minutes (45 minutes of structured exercise plus 15 minutes of structured patient education on vascular risk factor management and walking behavior). Treadmill exercise is initiated at 3.2 km/h on a flat gradient; participants walk until claudication pain reaches severity level 3 on a standardized four-point scale, then rest until pain subsides to level 1, repeating for five to six cycles per session.

Structured progression applies as follows: during weeks 1–4, treadmill speed increases by 0.3 km/h every two weeks to a maximum of 4.0 km/h; during weeks 5–8, treadmill grade increases by 1% every two weeks to a maximum of 3%. From week 5, resistance exercises targeting the major lower extremity muscle groups are added, beginning at two sets of 10 repetitions and progressing toward five sets at approximately 70% of one-repetition maximum. Session attendance is documented individually for each participant. Adequate adherence is defined as completion of ≥30 of 36 sessions (≥83%); non-adhering participants are retained in the primary analysis under intention-to-treat principles and analyzed separately in a pre-specified sensitivity analysis. Weekly telephone contact is maintained by a trained exercise physiologist to monitor symptoms and reinforce adherence. Participation in any other formal structured exercise program or rehabilitation intervention during the 12-week SET period is not permitted; habitual daily physical activity and unsupervised walking are allowed.

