The composite endpoint comprises four pre-specified outcome combinations, addressed as follows: The primary analysis of treatment failure includes three specific scenarios: (i) program non-completion, defined as failure to attend the requisite number of SET sessions, regardless of functional outcome; (ii) functional non-response among program completers, characterized by completion of the program without achieving the MWD threshold at three months (T1); and (iii) revascularization occurring within the three-month follow-up period, irrespective of functional outcome. This approach aligns with the protocol’s objective of identifying patients capable of deriving sufficient benefit from conservative management alone. The rationale for classifying revascularization as treatment failure, even when accompanied by functional improvement, is that such cases indicate the conservative management pathway was not maintained. Sensitivity analysis #6 (Table 3) examines the subset of guideline-concordant revascularization events separately.

The four pre-specified outcome combinations are: (1) functional improvement achieved AND revascularization-free = treatment success; (2) functional improvement not achieved AND revascularization occurred = treatment failure; (3) functional improvement achieved BUT revascularization occurred = classified as treatment failure in the primary analysis; this discordant case type (functional improvement with revascularization) will be specifically examined in sensitivity analysis #6 (Table 3), restricting to guideline-concordant revascularization events only, to assess whether revascularization was guideline-concordant or driven by patient preference; (4) functional improvement not achieved AND revascularization-free = treatment failure. Failure to meet either criterion (b) or the MWD threshold in (a) constitutes treatment failure.

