### Sample size

Sample size is determined primarily by the precision required for the primary model’s discrimination statistic [26, 27]. A minimum of 40 treatment failures is targeted for the five-predictor primary logistic regression model (muscle density, VAT area, age, sex, baseline MWD), yielding an events per variable (EPV) ratio of approximately 8. This EPV is recognized as modest, providing the primary rationale for the conservative four-predictor robustness check (Table 3, sensitivity analysis #7a). A supplementary power calculation confirms approximately 80% power to detect an odds ratio ≥2.0 per 10 HU decrease in skeletal muscle density (α ═ 0.05, two-tailed).

Assuming a treatment failure rate of 40%, reflecting the program non-completion component of the 40–50% failure rate reported in real-world European SET series [9] and a local institutional audit (approximately 38%); this 40% assumption captures both program non-completion and early revascularization combined, without separately modeling the functional non-response rate among completers. Accounting for 22% attrition from dropout and protocol non-completion, 128 patients must be enrolled to achieve 100 evaluable participants with 40 treatment failures. The IRONIC trial [8], which demonstrated that a significant proportion of claudicants managed conservatively required revascularization during follow-up, supports the clinical relevance of this failure rate, although it was not designed to quantify SET-specific non-response. A pre-specified sensitivity analysis reports model performance under a 30% failure rate scenario (approximately 30 failures, approximately 70% power). All precision-related conclusions are explicitly framed within the derivation cohort boundaries; external validation is necessary before any clinical translation.

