**Multiple imputation specification**: Missing data are addressed through multiple imputation by chained equations (MICE). All analysis variables—including the primary composite outcome, all five primary predictors, all covariates in the expanded model, and secondary outcomes—are incorporated into the MICE model. Twenty imputation datasets are generated (50 iterations per dataset), and estimates are pooled according to Rubin’s rules. Imputation diagnostics include convergence trace plots and comparisons of observed versus imputed variable distributions. A complete-case sensitivity analysis is pre-specified (Table 3, sensitivity analysis #15). For follow-up data potentially deviating from the missing-at-random assumption, pattern-mixture models and tipping-point analyses are pre-specified.

Cumulative incidence functions are reported alongside cause-specific hazard analyses. Pre-specified sensitivity analyses are detailed in Table 3. Component-separate analyses of the functional improvement component (excluding the revascularization criterion) and the revascularization-free survival component are designated as mandatory pre-specified secondary analyses (Table 3), not optional sensitivity analyses; these analyses isolate each failure mode and will be reported in the primary publication regardless of the primary composite outcome results.

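### The sample size counts SET non-completion both as a source of treatment failures and as attrition removed before failures are counted, so the 100 evaluable, 40 failures and EPV of 8 do not follow from the trial's own endpoint

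*Protocol article*

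**What the plan says.** The Sample size section sets an event target: "A minimum of 40 treatment failures is targeted for the five-predictor primary logistic regression model", "yielding an events per variable (EPV) ratio of approximately 8". It takes the failure rate from non-completion: "Assuming a treatment failure rate of 40%, reflecting the program non-completion component of the 40–50% failure rate reported in real-world European SET series". It adds that "this 40% assumption captures both program non-completion and early revascularization combined, without separately modeling the functional non-response rate among completers". It then applies an attrition allowance: "Accounting for 22% attrition from dropout and protocol non-completion, 128 patients must be enrolled to achieve 100 evaluable participants with 40 treatment failures".

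Four other places say what happens to patients who stop or do not finish SET:

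- **Primary outcome:** the first of three failure scenarios is "program non-completion, defined as failure to attend the requisite number of SET sessions, regardless of functional outcome".
- **SET:** "non-adhering participants are retained in the primary analysis under intention-to-treat principles".
- **Assessment schedule (notes to Table 4):** patients who withdraw before the three-month assessment are invited to a withdrawal visit, and its data enter the intention-to-treat analysis.
- **Statistical analysis (multiple imputation):** the primary composite is one of the variables in the imputation model. Complete-case analysis appears only as sensitivity analysis #15 in Table 3.

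**The concern.** The sentence on the failure rate and the sentence on attrition use the same group of patients for opposite purposes. In the first, non-completers are a main source of the failures. In the second, dropout and non-completion take patients out of the evaluable set, and the 40% is then applied to those who remain.

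The endpoint does not allow this. A non-completer is a failure whatever the treadmill shows, so the outcome is known without a three-month test and the patient is evaluable by definition.

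Two things are at stake. First, 40 failures is the basis for every EPV in the protocol (about 8, 10, 13–14 and 3–4) and for the supplementary power statement. Second, the Sample size section is where the protocol mentions an evaluable subset, and it describes that subset as what remains after non-completion. Read literally at analysis, that would select patients on a component of the outcome.

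**Working it through.** **Inputs (Sample size section unless noted).** Target failures 40; predictors 5; failure rate 40%; attrition 22%; enrolment 128. Predictor counts for the other models come from Table 3 and Statistical analysis: 4 (#7a), 3 (#7b) and about 12 (#14). The low-rate scenario is 30% (#13).

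**Step 1. Reproduce the plan's figures.**
- Evaluable patients: 40 / 0.40 = 100.
- Enrolment: 100 / 0.78 = 128.2, stated as 128 (128 × 0.78 = 99.8).
- EPV: 40 / 5 = 8.

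The arithmetic is sound. The question is who the 22% (128 × 0.22 = 28.2, about 28 patients) are.

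**Step 2. When the stated figures are right.** If the 28 have no determinable composite and the same 40% risk as the rest, they take 28 × 0.40 = 11.2 failures with them. That leaves 51.2 − 11.2 = 40 failures in 100. This needs the 28 to be neither programme dropouts nor non-completers.

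**Step 3. Follow the endpoint and analysis rules, with nobody removed.** Expected failures are 128 × 0.40 = 51.2, and 40 failures would need only 40 / 0.40 = 100 enrolled.

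| Quantity | Stated | With 51.2 failures |
|---|---|---|
| Five-predictor EPV | about 8 | 51.2 / 5 = 10.2 |
| Four-predictor EPV (#7a) | about 10 | 51.2 / 4 = 12.8 |
| Three-predictor EPV (#7b) | about 13–14 | 51.2 / 3 = 17.1 |
| Twelve-predictor EPV (#14) | about 3–4 | 51.2 / 12 = 4.3 |
| Failures at 30% (#13) | about 30 | 128 × 0.30 = 38.4 |

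**Step 4. Bounds under other readings.**
- The 40% is the rate among all 128, all 28 removed are non-completers, and they are excluded: 51.2 − 28 = 23.2 failures in 100, EPV 23.2 / 5 = 4.6. This is the extreme low case.
- The 40% holds in the other 100 and the 28 are non-completers kept as failures: 40 + 28 = 68 of 128 (53%), EPV 68 / 5 = 13.6.
- Half of the 28 are non-completers. If these 14 are kept, 114 are evaluable, with 114 × 0.40 = 45.6 to 40 + 14 = 54 failures. If they are excluded, 51.2 − 14 = 37.2 failures remain in 100.

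The protocol does not give the split of the 22%, so it does not fix which of these applies.

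**The case against.** The strongest reply is that the 22% is an ordinary allowance for patients without a usable outcome. The attrition sentence speaks of protocol non-completion and the endpoint of programme non-completion. On that reading the 28 finished SET but missed the three-month test, or withdrew consent to use of their data, and Step 2 shows that 128/100/40 then follows exactly. Planning on observed outcomes is also legitimate, since imputation does not create observed events. This much stands: a reader might infer that the stated combination is impossible, and it is not. But the text does not define the 22% this way. It names dropout, and dropout from SET is already a failure under the endpoint. Nothing in the document marks the change from programme to protocol as deliberate.

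Three further inferences are not supported:

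- **That the trial is underpowered, with about 23 failures.** That case needs all 28 to be non-completers and the analysts to exclude them. No analysis section tells them to, and the sections cited above say the opposite.
- **That 22% contradicts the 40–50% non-completion rate in the Introduction or the local audit figure of about 38%.** The gap suggests equally that the 22% is a different quantity, and the audit figure is not clearly labelled as non-completion.
- **That specific corrected power values can be given.** The protocol states no SD for muscle density. An unadjusted normal approximation, power = Φ(ln 2 × SD/10 × √(np(1 − p)) − 1.96), matches the stated 80% (n = 100, p = 0.40) at an SD of 8.25 HU. With the same SD it gives about 75% at p = 0.30, where the protocol states about 70%. The back-solved SD is therefore not a sound basis.

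**Conclusion.** The point holds as an inconsistency in the planning figures. Non-completion enters the failure rate and the attrition allowance in adjacent sentences, and the stated 100 evaluable, 40 failures and EPV of about 8 do not follow from the endpoint and analysis rules unless the 22% is confined to undeterminable outcomes.

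Following those rules with all 128 analysed gives about 51 failures and an EPV of about 10. This assumes that 40% is the rate among all enrolled and that no composite is undeterminable. On that basis the stated figures are conservative and the 40-failure minimum is not threatened. The figure of about 23 failures in 100 is an extreme lower bound, reached only if non-completers are excluded in practice.

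This should be fixed. It does not change the model, the endpoint or recruitment.

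**What to change.** In the Sample size section:

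1. Remove programme dropout and non-completion from the attrition allowance.
2. If an allowance is kept, limit it to participants whose composite truly cannot be determined, and state its size.
3. State that non-completers belong to the primary analysis set as treatment failures.
4. Recompute expected failures, EPVs and power from that set, and give the muscle-density SD behind the power figure.

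Carry the new figures into Statistical analysis, Table 3 (#7a, #7b, #13, #14) and the Discussion sentence that expects 40 failures. With no allowance these are about 51 failures, EPVs of about 10, 13, 17 and 4 for the five-, four-, three- and twelve-predictor models, and about 38 failures in the 30% scenario. Any allowance retained lowers them in proportion, if that loss is unrelated to outcome.

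The cost is one reworded paragraph and a recalculation. Enrolment stays at 128. It is best done before enrolment opens, planned for June 2026.

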### Blinding

This is an observational cohort study without randomization or treatment allocation. The CT analyst performing body composition segmentation is blinded to participant clinical outcomes. The vascular surgeon adjudicating revascularization events is blinded to body composition data and predictor values throughout the follow-up period. Disagreement resolution procedure: In cases where the adjudicating vascular surgeon cannot reach a clear classification (concordant versus non-concordant revascularization), a second independent vascular surgeon reviews all relevant clinical documentation while remaining blinded to body composition data. If disagreement persists after an independent second review, the case is resolved through consensus discussion between both adjudicators; the process and final classification are documented in the study log. Indeterminate cases after consensus are classified as non-concordant for the primary analysis and concordant in a pre-specified sensitivity analysis. Given the observational, non-interventional nature of this study and the absence of experimental treatment allocation, no independent data monitoring committee is established; no interim analyses or stopping rules are pre-specified.

### Statistical analysis

**Analytical hierarchy:** In all primary analyses (H1 and H2), skeletal muscle density and VAT area are treated as continuous standardized z-scores (mean = 0, SD = 1). This approach serves as the foundation for all inferential conclusions. All classification thresholds—whether derived from cohorts via Youden index maximization (cutpointr) or from literature pertaining to non-PAD populations (Martin et al. [21]; general population VAT reference values [23, 24])—are established post-hoc and are explicitly designated as exploratory and hypothesis-generating. These thresholds do not influence the primary predictive model and necessitate external validation in an independent PAD cohort prior to any clinical application. This distinction is consistently maintained throughout the statistical analysis section.

All analyses are conducted using International Business Machines (IBM) Statistical Package for the Social Sciences (SPSS) Statistics, version 30 (IBM Corp., Armonk, NY) and R version 4.3 (R Foundation for Statistical Computing, Vienna, Austria; packages: rms, cmprsk, mice, boot, cutpointr, survminer). The complete statistical analysis plan is pre-registered at ClinicalTrials.gov before database lock, and no post-hoc modifications to the primary analysis are allowed.

**Primary model specification:** The primary model for H1 and H2 is a pre-specified multivariable logistic regression with binary treatment success (success/failure) as the outcome, incorporating five predictors: skeletal muscle density (continuous standardized z-score), VAT area (continuous standardized z-score), age (continuous), sex (binary), and baseline MWD (continuous). SMI and SAT are excluded from the primary model; they are included only as covariates in the pre-specified secondary expanded model. This model specification is fixed and will not be altered once data collection begins.

The two co-primary hypotheses (H1, H2) are tested at a Bonferroni-corrected significance threshold of p < 0.025 per hypothesis (family-wise α ═ 0.05). Hypothesis 3 (H3), pertaining to sarcopenic obesity, is classified as a secondary/descriptive hypothesis and is not subject to family-wise correction. Secondary Spearman correlation analyses between continuous body composition parameters and secondary functional outcomes will be reported with Benjamini-Hochberg false discovery rate correction (q < 0.05).

**Continuous predictor modeling**: In the primary model, skeletal muscle density and VAT area are utilized as continuous standardized z-scores. The nonlinearity of each continuous predictor is assessed using restricted cubic splines, with three to five knots selected based on the Akaike Information Criterion. Exploratory cutpoint derivation employing the Youden index (implemented via cutpointr) is conducted as a separate secondary exploratory analysis and is clearly labeled as hypothesis-generating; derived thresholds are not employed in the primary predictive model.

Internal validation is performed using bootstrap resampling (1000 samples), yielding optimism-corrected area under the curve (AUC), calibration slope, and calibration-in-the-large. The bootstrap resampling procedure encompasses the entire analytical pipeline, including nonlinearity assessment (spline knot selection); the same bootstrap samples are utilized for optimism correction across the full pipeline. For any exploratory cutpoint derivation, the derivation step is nested within a distinct independent bootstrap loop to prevent double-counting of optimism. A four-predictor model excluding baseline MWD (skeletal muscle density, VAT area, age, sex; EPV approximately 10) is included as a pre-specified robustness check (Table 3, sensitivity analysis #7a). A three-predictor model excluding sex (EPV approximately 13–14) is also part of the pre-specified robustness checks. For H3, the four-group sarcopenic obesity classification is incorporated as a categorical predictor in a similar model; H3 analyses are reported descriptively and interpreted as exploratory.

**Pre-specified secondary expanded model:** A secondary expanded confounding model is pre-specified, adjusting for the five primary predictors along with additional variables: ABI (continuous), smoking status (categorical), diabetes mellitus (binary), Clinical Frailty Scale score (ordinal), TASC II classification (categorical), SMI (continuous standardized z-score), and SAT area (continuous standardized z-score). This expanded model comprises approximately 12 predictors and, with 40 expected events, yields an EPV of approximately 3–4; this EPV limitation designates the expanded model as a robustness sensitivity analysis rather than a primary inferential tool (Table 3, sensitivity analysis #14). Results will be reported with 95% confidence intervals and interpreted cautiously due to limited EPV.

**Multiple imputation specification**: Missing data are addressed through multiple imputation by chained equations (MICE). All analysis variables—including the primary composite outcome, all five primary predictors, all covariates in the expanded model, and secondary outcomes—are incorporated into the MICE model. Twenty imputation datasets are generated (50 iterations per dataset), and estimates are pooled according to Rubin’s rules. Imputation diagnostics include convergence trace plots and comparisons of observed versus imputed variable distributions. A complete-case sensitivity analysis is pre-specified (Table 3, sensitivity analysis #15). For follow-up data potentially deviating from the missing-at-random assumption, pattern-mixture models and tipping-point analyses are pre-specified.

Cumulative incidence functions are reported alongside cause-specific hazard analyses. Pre-specified sensitivity analyses are detailed in Table 3. Component-separate analyses of the functional improvement component (excluding the revascularization criterion) and the revascularization-free survival component are designated as mandatory pre-specified secondary analyses (Table 3), not optional sensitivity analyses; these analyses isolate each failure mode and will be reported in the primary publication regardless of the primary composite outcome results.

Classification thresholds for the primary predictors (skeletal muscle density for H1; VAT area for H2) will be derived prospectively within this cohort and treated as pre-specified study outcomes rather than assumptions. For the binary primary composite outcome, optimal cut-points will be identified by maximizing the Youden index (J = sensitivity + specificity -- 1) using the cutpointr R package; 95% confidence intervals will be obtained via 1000-sample bootstrap resampling. Separate derivations will be conducted for skeletal muscle density (single threshold) and VAT area (sex-stratified: men and women analyzed independently to account for dimorphic adipose tissue distribution). For the secondary time-to-revascularization outcome, optimal cut-points will also be identified by maximizing the log-rank statistic via survminer::surv_cutpoint(), providing a time-to-event-appropriate complement to the Youden-index approach. Each threshold derivation will report the optimal cut-point value, Youden index, sensitivity, specificity, and 95% bootstrap CI. As thresholds will be derived from the same cohort used for evaluation, internal optimism is anticipated and explicitly acknowledged. Thus, all threshold-based classification results will be interpreted within the derivation-cohort framework, with external validation in an independent PAD multicenter cohort as the pre-specified mandatory next step prior to clinical translation. Literature-derived thresholds from non-PAD populations will be retained as pre-specified sensitivity analyses (Table 3) to facilitate transparent cross-referencing with existing oncological and metabolic literature.

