The primary aim of this study is to determine whether L3 CT-derived skeletal muscle density and VAT area independently predict composite SET treatment success at three months in patients with Fontaine IIa–IIb intermittent claudication. Two co-primary hypotheses are tested: H1 proposes that lower skeletal muscle density per 1 standard deviation (SD) decrease will predict treatment failure; H2 posits that higher VAT area per 1 SD increase will predict treatment failure. H3, which states that the sarcopenic obesity phenotype is associated with the lowest treatment success rates across body composition phenotype groups, is designated as a secondary/descriptive hypothesis and is not included in the family-wise Bonferroni correction for the co-primary analyses. This is a prospective observational derivation cohort study, hereafter referred to as CT Body Composition as Predictor of Exercise Therapy Outcome in PAD (COMPOSE-PAD); external multicenter validation is the pre-specified and required next step before clinical translation.

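### The bootstrap validation replays AIC spline-knot selection although the primary model is fixed at five single terms, so taken literally it corrects a more flexible procedure than the model reported

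*Protocol article*

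**What the plan says.** Under Statistical analysis (primary model specification) the five predictors are "skeletal muscle density (continuous standardized z-score), VAT area (continuous standardized z-score), age (continuous), sex (binary), and baseline MWD (continuous"). The article adds "This model specification is fixed and will not be altered once data collection begins" and, a little earlier, "no post-hoc modifications to the primary analysis are allowed".

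Three other places fit this form. The Introduction words the hypotheses on a per-SD scale: "H1 proposes that lower skeletal muscle density per 1 standard deviation (SD) decrease will predict treatment failure", and "H2 posits that higher VAT area per 1 SD increase will predict treatment failure". Sample size targets 40 failures for the five-predictor model, "yielding an events per variable (EPV) ratio of approximately 8". The body composition section says z-scores were chosen so that the effect estimates can be compared on one scale.

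The continuous predictor modelling paragraph then adds: "The nonlinearity of each continuous predictor is assessed using restricted cubic splines, with three to five knots selected based on the Akaike Information Criterion". The next paragraph describes the 1000-sample bootstrap that gives the corrected AUC and the two calibration measures: "The bootstrap resampling procedure encompasses the entire analytical pipeline, including nonlinearity assessment (spline knot selection"). The strengths paragraph of the Discussion lists the spline step again as part of the validation.

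Cut-point derivation is treated differently. It is kept out of the primary model and given a bootstrap loop of its own. Splines receive neither statement.

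**The concern.** A bootstrap optimism correction is valid for the procedure that is replayed in each resample. The model to be reported has one term for each CT predictor, while the replayed procedure is said to include choosing three to five knots by AIC. The article does not say whether the knot choice can change the fitted model, or which fitted model the corrected performance describes.

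An analyst who follows the text literally would fit the AIC-chosen splines in every resample and subtract the resulting optimism from the apparent performance of the five-term model. Discrimination and calibration would then look worse than they are. These are the main performance outputs, and the Sample size section rests the study size mainly on the precision of the discrimination statistic.

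**Working it through.** **1. The plan's own figure.** Events per variable = 40 failures / 5 predictors = 8.0. This reproduces the stated value and holds only with one parameter per predictor. The robustness models agree: 40/4 = 10 and 40/3 = 13.3.

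**2. Parameter count with splines.** A restricted cubic spline with k knots uses k − 1 parameters.

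| Knots | CT predictors only: 3 + 2(k − 1) | 40 / parameters | All four continuous predictors: 1 + 4(k − 1) | 40 / parameters |
|---|---|---|---|---|
| 3 | 7 | 5.7 | 9 | 4.4 |
| 4 | 9 | 4.4 | 13 | 3.1 |
| 5 | 11 | 3.6 | 17 | 2.4 |

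**3. AUC optimism, fixed model against spline selection.** The documents give no effect sizes for this, so the effects are assumed. Every set-up has 100 patients, about 40% failures and splines on the two CT predictors.

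| Set-up | Fixed model | With AIC selection | Difference |
|---|---|---|---|
| A: 400 cohorts, test sets of 4,000, true AUC about 0.68 | 0.057 | 0.086 | 0.029 |
| B: 60 cohorts × 40 resamples | 0.058 | 0.095 (linear also a candidate); 0.100 (3 to 5 knots only) | 0.037; 0.042 |
| C: a further run under assumed effects | 0.063 | 0.104 to 0.114 | 0.041 to 0.051 |

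Set-up B used independent predictors. The log-odds ratios were −0.45 (muscle density), 0.45 (VAT), 0.2 (age), 0.1 (sex) and −0.3 (baseline walking distance).

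In set-up B the fixed model had an apparent AUC of 0.718 and a true AUC of 0.662. Subtracting its own optimism gives 0.659. Subtracting the spline procedure's optimism gives 0.617 to 0.622, about 0.04 too low. (These are averages before rounding, so the last digit can differ from subtraction of the rounded values.)

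The calibration slope shifts the same way: 0.72 against 0.59 in set-up A, and 0.69 against 0.51 to 0.53 in set-up B. In set-up A, splining all four continuous predictors gave optimism of 0.117, a difference of 0.117 − 0.057 = 0.060.

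**4. If the AIC-chosen form were tested instead.** H1 was simulated with no effect of muscle density and tested at 0.025.

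| Set-up | Fixed term | AIC-chosen form |
|---|---|---|
| A: 3,000 cohorts | 3.3% | 7.6% |
| B: 2,000 cohorts | 2.75% | 9.1% (linear also a candidate); 7.9% (3 to 5 knots only) |
| C | 2.6% | 7.6 to 8.2% |

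In these null cohorts of set-up B, where each CT effect was truly linear or null, AIC still replaced at least one CT term by a spline in about 51% of data sets when linear was a candidate.

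**The case against.** The strongest reply is that the primary specification already settles the matter. The z-scores are named as the basis for inference, the model is declared fixed, and nonlinearity is only said to be assessed. If the spline step is a diagnostic, every resample still ends in the five-term model, the optimism is that of the five-term model, and nothing is over-corrected. If splines did enter the model, replaying the knot choice would be the correct safeguard. Set-up B supports this: the spline procedure, corrected with its own optimism, gives 0.640 to 0.643 against a true 0.645 to 0.651. The Discussion also concedes limited precision for discrimination, and a full analysis plan exists that is not shown.

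Much of this stands. A reader might infer that the results are wrong whichever way the text is read, that the H1 and H2 tests are data-driven, or that the stated events per variable is mistaken. The documents do not support any of these. The fixed specification rules out splines replacing the tested terms, about 8 is right for that model, and a purely diagnostic replay would leave the correction sound.

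What does not stand is that the point can be left to the analysis plan. The article itself states the bootstrap rule, names knot selection as part of it and claims it as a strength. Under the diagnostic reading that mention would have no effect on the correction. The article draws the needed separation for cut-points but not for splines.

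**Conclusion.** The stated validation rule does not match the fixed primary model and should be corrected. Taken literally, it over-corrects the AUC of the five-term model by roughly 0.03 to 0.05, and the calibration slope in the same direction. It is harmless only if the spline step never changes the model fitted in each resample, which the article does not say.

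The effects on H1 and H2 are conditional. They arise only if AIC-chosen splines are let into the model, contrary to the fixed specification. In that case there is no single per-SD odds ratio, type I error is about 8 to 9% against 2.5%, and events per parameter are 3.6 to 5.7 with splines on the CT predictors alone.

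The parameter counts are exact. The simulated sizes rest on assumed effects (with independent predictors in set-up B), and the optimism figures of set-up B come from only 60 cohorts. Part of the type I excess is small-sample inflation of the likelihood-ratio test, as the values of 2.6 to 3.3% for the fixed term suggest. Direction and rough size are what can be relied on. That one term per CT predictor means a linear term is inferred from the z-score terms, the per-SD hypotheses and the events-per-variable count, which all agree.

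**What to change.** - State that the primary optimism correction (AUC, calibration slope and calibration-in-the-large) bootstraps exactly the fixed five-term model.
- State that H1 and H2 remain one-degree-of-freedom tests of the z-score terms whatever the spline assessment shows.
- Move the spline assessment to a labelled secondary analysis with its own bootstrap loop, as is already done for cut-points, and report its events per parameter from the actual parameter count.
- Amend the strengths paragraph of the Discussion to match.
- Optionally, replace the AIC search by a single pre-set three-knot spline for each CT predictor.

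The cost is a few sentences and no additional data. The change should be made before enrolment, planned for June 2026, because the article bars changes to the model once data collection begins. The downside is that a marked nonlinearity would appear only in the secondary analysis.
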